### Data collection and analysis

#### Medical profile, post-COVID-19 symptoms, and blood collection

Participants were scheduled for same day comprehensive testing inclusive of a medical review, functional performance, blood collection and imaging (Figure 1).

**Figure 1 fig1:**
[figure not shown]
Schema of study design. Upper panel depicts recruitment of patients with recovered COVID-19 and healthy controls without prior COVID-19. Middle panel depicts functional testing, blood collection and magnetic resonance imaging for all participants. Functional testing included Brief Smell Identification Testing (B-SIT), 6 min walk testing, cognitive testing on a tablet with NIH toolbox and spirometry. Bottom panel depicts collection of clinical outcomes at 12 months. CBC, complete blood count; AST, aspartate aminotransferase; ALT, alanine aminotransferase; LDH, lactate dehydrogenase; GGT, gamma-glutamyl transferase; LVEF, left ventricular ejection fraction; DTI, diffusion tensor imaging.

A detailed assessment of relevant medical history and medication use was achieved through direct questioning and a review of health records. In patients with recovered COVID-19, data on the timing and duration of illness, the need for hospitalization and transfer to intensive care were recorded.

At the time of study-related functional assessments and MRI, patients with recovered COVID-19 were screened for the presence of long COVID related symptoms including fatigue, cognitive impairment, shortness of breath, chest pain and palpitations using a standardized questionnaire. Additionally, patients rated the overall impact of these symptoms on their daily activities using a 5-point scale ranging from 1 (no limitations) to 5 (severely limited).

Blood pressure, heart rate and oxygen saturation were measured on all participants and blood work was performed to assess for circulating biomarkers of inflammation (c-reactive protein, white blood cell count with differential and d-dimer), end organ damage (high sensitivity cardiac troponin I, b-type natriuretic peptide, creatinine and hepatic enzymes) and cardiometabolic profile (glucose, insulin and lipid profile). Blood biospecimens were also stored in a research biobank (Canadian BioSample Repository) for future analysis.

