The prevailing etiologic mechanisms proposed for long COVID include immune dysregulation, autoimmunity and immune imprinting, endothelial dysfunction and thrombosis, impaired neurological signaling and effects on the host microbiome (10). However, knowledge on pathogenesis remains limited and there is an important unmet need for rigorous preclinical and clinical studies in long COVID. Given the systemic (i.e., multi-organ) nature of both acute phase COVID-19 illness and long COVID, knowledge has been gained from whole body imaging. Magnetic resonance imaging (MRI) is a safe (non-ionizing radiation), non-invasive imaging technique that provides detailed information on tissue changes including injury. MRI has been used as an alternative to computed tomography for the characterization of pulmonary disease following severe COVID-19 pneumonia (11). MRI derived measures of visceral adipose tissue and liver fat are also strongly associated with risk of hospitalization from COVID-19 independent of body mass index (12). Whole body MRI-based studies of patients with recovered COVID-19 have identified subclinical multi-organ involvement (13–15). In an MRI study of 201 patients with long COVID, mean age 45 years, organ damage was identified in 70%, including the pancreas in 45%, liver in 29% and heart in 24% (14). In this study, MRI evidence of organ impairment was defined as a non-contrast T1 time (longitudinal relaxation time) greater than normal reference values. Several cardiac MRI based studies of patients with recovered COVID-19 have found evidence of subclinical myocardial inflammation (16–18), however, the clinical significance of this finding is not well established.

We undertook a multicenter, prospective study of patients in Alberta with recovered COVID-19 from October 2020 to August 2021 to characterize symptom burden, functional impairment and end-organ damage by MRI. We hypothesized that the extent of tissue injury on MRI would be associated with patient reported disability and objective measures of functional performance.

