### Participant selection

Adult patients within 3 months of COVID-19 illness and prior to the availability of m-RNA vaccination, were recruited from October 2020 to July 2021. Patients with COVID-19 illness requiring hospitalization were identified prospectively at the University of Alberta hospital and retrospectively by the regional health authority, Alberta Health Services. Interested patients with less severe COVID-19 illness also contacted the study team following advertisement on the internet, mainstream media and personal communication. All patients required documentation of COVID-19 infection on nasal or oropharyngeal swab polymerase chain reaction testing within the last 6 months. Healthy controls without prior COVID-19 infection were also recruited from July 2021 to July 2023. Normative brain imaging and cognitive testing were collected separately from healthy control participants prior to the pandemic (19). Control participants with a history of cardiovascular disease or cardiovascular risk factors were excluded. No participants had contraindication to MRI and all provided informed consent after a review of the study objectives, procedures and potential risks and benefits.

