### Statistical plan

The Shapiro–Wilk normality test will be used to test the normal distribution of continuous variables which will be expressed as mean ± standard deviation or median (25th, 75th percentile), as appropriate. Categorical variables will be expressed as frequency and percentage. When comparing data between recovered COVID-19 patients and healthy controls, chi-square testing or Fisher’s exact test will be used for categorical variables and two sample t-test or Mann–Whitney U test used for continuous variables, as appropriate. Functional performance, biomarker results and imaging metrics indicative of organ injury will be compared across groups of symptom severity (none, mild, moderate and severe) within the recovered COVID-19 patients using a one-way analysis of variance with *post hoc* pairwise comparisons by either Tukey’s or Games-Howell tests, depending on equality of variances. Pearson correlation analyses will evaluate relationships between MRI measures of tissue injury and functional performance metrics. Univariable Cox proportional regression of clinical outcome will be performed in all serum and imaging parameters. In the multivariable Cox proportional hazard analysis, all non-collinear parameters of interest with univariable *p*-value < 0.2 will independently test for their association with composite outcome after adjustment for baseline risk. A *p* value less than 0.05 will be considered significant for all tests.

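### Comparisons among recovered patients are unadjusted for pre-existing disease, so COPD (23 of 215) can produce a lung injury association that is read as post-COVID

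*Protocol article*

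**What the plan says.** All places are in the protocol article.

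- **Entry (Participant selection).** For patients the stated requirement is infection: "All patients required documentation of COVID-19 infection on nasal or oropharyngeal swab polymerase chain reaction testing within the last 6 months". The comorbidity exclusion is worded for the other arm only: "Control participants with a history of cardiovascular disease or cardiovascular risk factors were excluded".
- **Prior disease among the 215 patients (Table 3).** COPD 23, sleep apnea 14, stroke 5, cognitive impairment 3, neuropathy 7, coronary artery disease 4, heart failure 1, atrial fibrillation 4, renal insufficiency 7, liver disease 0. Hypertension (51) and diabetes (28) are more common.
- **Symptoms (Medical profile, post-COVID-19 symptoms, and blood collection).** "patients with recovered COVID-19 were screened for the presence of long COVID related symptoms including fatigue, cognitive impairment, shortness of breath", and "patients rated the overall impact of these symptoms on their daily activities using a 5-point scale". No pre-illness reference is described. Prior history is available: "A detailed assessment of relevant medical history and medication use was achieved through direct questioning and a review of health records".
- **Outcomes (Table 1).** Spirometry, the 6 min walk, lung water density and radiomic lung lesions are listed as lung injury outcomes.
- **Analysis (Statistical plan).** Organ measures are compared across symptom-severity groups "within the recovered COVID-19 patients using a one-way analysis of variance with" post hoc pairwise tests. MRI and functional measures are related by Pearson correlation. Adjustment for baseline risk is stated only for the Cox model of clinical outcome.
- **Hypothesis (Introduction).** The study expects that "the extent of tissue injury on MRI would be associated with patient reported disability" and with objective functional performance.

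**The concern.** The two analyses that test the hypothesis are between-person comparisons among recovered patients. A patient with long-standing COPD may be breathless and limited in daily activity, and may also have poor spirometry, a short walk and an abnormal lung MRI, all for reasons that predate infection. That patient adds to the association between symptoms and lung injury, and to the association between lung MRI and function, whatever COVID-19 did.

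This is ordinary confounding by a common cause inside the patient group. It is separate from the imbalance between patients and controls, and better-matched controls would not remove it. The Discussion intends the results to inform mechanisms and therapeutic targets for long COVID. An association produced by old lung disease would point to the wrong target.

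**Working it through.** **1. The plan's own figure.** COPD: 23/215 = 10.7%, printed as 11% in Table 3. It reproduces.

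**2. Inputs.** From the documents: n = 215, COPD proportion p = 23/215, alpha 0.05 (two-sided assumed). Not in the documents, so assumed: the shift d (in SD) that COPD causes in a measure, the symptom-group sizes, and the share of COPD patients in the moderate or severe groups. All scenarios assume no COVID-related association.

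**3. ANOVA across four symptom groups.** Assume 30% of patients without COPD are in the moderate or severe groups, against 50% or 70% of those with COPD. The share with COPD is then:

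- 50% case, moderate/severe: 0.107 × 0.5 / (0.107 × 0.5 + 0.893 × 0.3) = 16.6%; none/mild: 7.9%; gap 0.088.
- 70% case, moderate/severe: 21.9%; none/mild: 4.9%; gap 0.170.

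The spurious mean difference is gap × d. It runs from 0.088 × 1 = 0.09 SD to 0.170 × 2 = 0.34 SD over d = 1 to 2. Simulated rejection rates, repeated independently with agreement to within about 1 percentage point:

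| d (SD) | 50% case | 70% case |
|---|---|---|
| 0.5 | 5% | 7% |
| 1.0 | 7% | 14% |
| 1.5 | 9% | 24% |
| 2.0 | 12% | 37% |

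The rates depend heavily on how strongly COPD drives the symptom rating. In another model COPD shifts an underlying symptom score by the same d, with groups of 40/35/15/10%. The rates are then about 6%, 18%, 69% and 99% for the same four shifts.

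**4. Pearson correlation of MRI with function.** If COPD shifts both measures by d, the induced correlation is r = p(1−p)d² / (1 + p(1−p)d²), with p(1−p) = 0.0955. The rejection rate follows from Fisher's z: atanh(r) × √212 against 1.96.

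| d (SD) | r | atanh(r) × √212 | Rejection rate |
|---|---|---|---|
| 0.5 | 0.023 | 0.34 | 6% |
| 1.0 | 0.087 | 1.27 | 25% |
| 1.5 | 0.177 | 2.60 | 74% |
| 2.0 | 0.276 | 4.13 | 98% |

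**5. Other organs.** Direct prior disease affects at most 4 + 1 + 4 = 9 patients for heart, 5 + 3 = 8 for brain, 7 for kidney and 0 for liver, if no one is counted twice. The ANOVA model of step 3 with the heart, brain and kidney counts gives 5–7% in the 50% case and 6–11% in the 70% case for 1–2 SD. It reaches 10–11% only at 2 SD, and is about 5% at 0.5 SD.

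**6. Precision without the COPD patients.** n = 215 − 23 = 192. The correlation detectable with 80% power is tanh((1.960 + 0.842)/√(n−3)): 0.190 at n = 215 and 0.201 at n = 192.

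**The case against.** - **The size is assumed.** This stands. The documents give no COPD effect on any measure, no symptom-group sizes and no symptom rate in COPD. At 0.5 SD the bias is negligible. In the simulations, dropping COPD returns the error rate to about 5%, but only because COPD is the sole source of association there. It does not show that exclusion would remove all confounding in the real data.
- **It is a lung point.** This largely stands. A reader might infer that every organ analysis is compromised. The Table 3 counts do not support that for heart, brain or kidney except under extreme shifts, nor for liver through direct prior disease. Hypertension and diabetes could act in a similar way on cardiac and renal measures, but that was not quantified.
- **The questionnaire may ask about onset.** It may. It is described as standardized and is not shown. A reader might infer that long-standing symptoms were knowingly counted as long COVID. The article does not show this, and it labels the groups by symptom severity, not as long COVID categories. What remains is that the stated analysis makes no use of onset.
- **A full analysis plan may add covariates or sensitivity sets.** Possibly. But the article names the test for each comparison and states adjustment for one model only, so the point is about what is fixed and not about missing detail.
- **There is no pre-infection scan.** That is inherent in a study registered as late cross-sectional, and it is not an error.
- **Excluding prior disease need not be the main analysis.** Agreed. Covariate adjustment keeps all 215 patients and the intended population.

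**Conclusion.** The concern holds for the lung and 6 min walk outcomes. The symptom-severity ANOVA and the MRI–function correlations are specified without adjustment, in a patient group that includes 23 people with COPD and whose symptoms have no stated link to onset after infection. Followed as written, the plan allows pre-existing lung disease to appear as post-COVID lung injury. The false-positive rate could be close to nominal (0.5 SD) or well above it (from about 1 SD, especially for the correlations). These figures illustrate the mechanism under assumed effects and do not estimate the bias in this cohort. They do not show that any association the study finds will be false. For heart, brain and kidney the same mechanism exists, but with few affected patients. The point merits a change to the analysis, not to the design.

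**What to change.** 1. **Lung and 6 min walk outcomes.** Replace the unadjusted ANOVA with a linear model on symptom-severity group, and the Pearson correlation with a partial correlation. Adjust both for documented COPD, age, sex and smoking.
2. **Repeat both without the 23 COPD patients (n = 192)**, and report the two sets of results side by side.
3. **Heart, brain and kidney.** Add a sensitivity analysis excluding patients with direct prior disease of that organ (at most 9, 8 and 7).
4. **Wording.** Describe symptoms as present at 3–6 months unless the questionnaire or health records show that they were new or worse since infection. If the questionnaire records onset, say so and use it.

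**Cost.** The covariates are already collected (Table 3), so no new data are needed. Adjustment uses a few degrees of freedom. The restricted lung analysis loses little precision (detectable correlation 0.190 to 0.201).

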### Functional assessments

Standardized testing to evaluate olfaction, cognition, lung function and functional capacity was administered by trained research personnel. Smell was evaluated using the Brief Smell Identification Test (BSIT) which requires the identification of 12 odors from a scratchable booklet. In healthy older individuals, impaired olfaction on BSIT predicts cognitive decline (20). Cognitive performance was ascertained during 30–40 min sessions from the NIH toolbox with patients completing 5 modules including the Picture Sequence Memory Test, List Sorting Working Memory Test, Dimensional Change Card Sort Test, Auditory Verbal Learning Test and Oral Symbol Digit Test. Hand-held spirometry measured forced expiratory volume in 1 s and forced vital capacity during 3 repetitions. Six-minute walk test (6MWT) was performed to assess aerobic endurance using standardized instructions (21). Patients also performed a 25-foot timed walk test to identify potential neurologic disease affecting mobility (22).

### Magnetic resonance imaging

A multiparametric, non-contrast research MRI was performed at 3 T (Magnetom Prisma, Siemens Healthineers) at the Universities of Alberta and Calgary with a total scan time of approximately 75 min (Figure 2). Image analysis for cardiac and non-cardiac data was performed at core lab facilities within the University of Calgary and University of Alberta, respectively.

**Figure 2 fig2:**
[figure not shown]
Representative magnetic resonance images of multiple organs are shown for. Brain: Volumes with T1, lesions with FLAIR, white matter connectivity with DTI, and iron/myelin indication with QSM/R2* sequences. Lungs: Parenchyma lung water density quantification using free-breathing yarnball sequence. Heart: Structure, function from cine imaging and T1 and T2 mapping sequences. Body Composition: Abdominal fat/water separated imaging with chemical-shift encoded approach (multi-echo gradient echo sequence). Liver: PDFF, water-specific T1 and T2* using a SR-CSE sequence. Kidney: T1 mapping using the MOLLI sequence. Skeletal Muscle: PDFF, water-specific T1 and T2* with calculation of fat and muscle volumes and muscle T1.

*Cardiac*: Standard imaging sequences were used to assess cardiac structure and function. Steady-state free precession cine imaging was acquired with retrospective ECG gating with full left and right ventricular coverage. Typical acquisition parameters were 1.09 ms echo time, 2.53 ms repetition time, 30° flip angle, 8 mm slice thickness with a 2 mm gap, field of view 400 × 300 mm, acquisition matrix 256 × 144, 1,500 Hz/pixel, 15 views per segment, rate 3 parallel imaging (GRAPPA), and 30 reconstructed cardiac phases. Native myocardial T1 mapping was acquired using the modified Look-Locker inversion recovery (MOLLI) sequence (23) from a single mid ventricular short axis slice with typical parameters: 0.89 ms echo time, 2.47 ms repetition time, 35° flip angle, 8 mm slice thickness, field of view 410 × 330 mm, acquisition matrix 224 × 140, 1,395 Hz/pixel, rate 2 parallel imaging (GRAPPA), 5(3)3 protocol. T2 mapping was acquired with matching slice location, field of view, resolution and flip angle with a 1.19 ms echo time and 2.77 ms repetition time.

Ventricular volumes, mass, ejection fraction, global longitudinal strain and myocardial T1 will be derived using commercially available software (cvi42, Version 5.13, Circle, Calgary, Canada). Regional myocardial T1 and T2 was measured in 6 equal segments from the mid ventricular slice.

*Body Composition*: A chemical-shift encoded acquisition enabled the generation of fat and water separated images with transverse slice prescriptions centered on the third lumbar vertebra (L3) (24). Typical image parameters included 8 axial slices with a 6 mm thickness, [1.65, 3.61, 5.57, 7.53, 9.49, 11.45] ms echo times, 13.1 ms repetition time, 30° flip angle, rate 2 parallel imaging (GRAPPA) for an 8 s end-expiration breath-hold acquisition with a subset of 3 images selected for analysis (25). For the body composition analysis, the volumes of skeletal muscle, intermuscular, visceral, and subcutaneous fat from contiguous axial slices will be measured using custom fully automated machine learning segmentation. Muscle and fat volumes from a cross-section at L3 have been shown to be accurate relative to cadaver measurements and representative of whole-body composition (26, 27).

*Liver*: Liver T1 and proton density fat fraction (PDFF) was acquired using a water-specific T1 mapping approach to eliminate systematic T1 errors from liver fat using a saturation-recovery chemical-shift encoded (SR-CSE) technique (28–30). Typical image parameters include 3 axial slices with a 6 mm thickness, [1.09, 2.45, 3.81, 5.17, 6.53, 7.89] ms echo times, 9.2 ms repetition time, 13° flip angle, rate 2 parallel imaging (GRAPPA) for a 6 s breath-hold acquisition. The liver will be manually traced on all three slices using custom software, with automated removal of blood vessels, with calculation of median T1, PDFF and T2* values as previously described (30).

*Kidney*: T1 mapping of the kidneys was acquired using the MOLLI sequence from a single coronal slice prescribed through the maximum cross-sectional area of both kidneys. Typical acquisition parameters: 0.98 ms echo time, 2.63 ms repetition time, 35° flip angle, 6 mm slice thickness, field of view 450 × 330 mm, acquisition matrix 224 × 144, 1,395 Hz/pixel, rate 2 parallel imaging (GRAPPA), 5(3)3 protocol. Custom software will be used to trace a line along the length of the renal cortex to select intersecting pixels, and circular regions of interest will be selected in renal medulla.

*Skeletal Muscle*: Skeletal muscle T1 and fat content (intermuscular, intramuscular, and subcutaneous) was measured using a muscle-specific variant of the SR-CSE approach. Typical image parameters include 5 axial slices (centered 17 cm superior to the distal head of the femur) with a 3.5 mm thickness (12.5 mm gap), [2.51 3.51 4.51 4.78 5.78 6.78] ms echo times, 9.0 ms repetition time, 30° flip angle, rate 2 parallel imaging (GRAPPA) for a 41 s acquisition. A custom machine learning segmentation approach will be used to identify subcutaneous fat, intermuscular fat, muscle and bone regions. Calculated parameters included volumes of subcutaneous fat, muscle, intermuscular fat, intramuscular fat (fat content in the muscle region), muscle T1 and muscle T2* (from the muscle region).

*Lungs*: Lung images were acquired using a custom non-Cartesian ultrashort TE (TE = 70 μs) yarnball *k*-space trajectory with free-breathing acquisitions (31). Free-breathing data collection was completed in 120 s with reconstruction of 2 mm × 2 mm × 2 mm resolution images at 20 respiratory phases over the breathing cycle. Global lung water density at functional residual capacity (minimum lung volume) was quantified with a user-independent machine learning lung segmentation approach. Additionally, the presence of patchy pathology was identified using an automated quantitative approach employing radiomic analysis of the lung parenchyma. We used a previously trained deep learning model to segment the lung parenchyma of our images (32). Once the parenchyma of each lung is isolated, intensities are discretized into 5% lung water density bins to simplify image features prior to feature extraction. Finally, 40 radiomic texture features are computed in three dimensions for each lung using a MATLAB (MathWorks, Natick, MA) toolkit (33).

*Brain*: After repositioning the participant into a 64 channel head RF coil, four different images were acquired of the brain over 24 min: (i) 3D fluid attenuation inversion recovery (FLAIR) for lesion detection (1.0 mm isotropic, 5 min), (ii) 3D T1-weighted MPRAGE for regional brain volumes (0.85 mm isotropic, 3.5 min), (iii) 2D high-resolution diffusion tensor imaging (DTI) for identifying strokes/cytotoxic edema and microstructure in white matter mainly (1.5 mm isotropic, 10 b0/6 b500/20 b1000/64 b2500 s/mm^2^, 9.5 min), and 3D multi-echo, gradient recalled echo (0.9 × 0.9 × 1.7 mm^3^, 6 TE from 3.8–31 ms, 5.5 min) for quantitative susceptibility mapping (QSM) and transverse relaxation rate (R2*) for micro-bleeds and sensitivity to iron/myelin, particularly in deep gray matter. The latter three images match previous protocols of a healthy cohort (19).

